### Guidance and adherence monitoring

eCoaches support the participants throughout the training by providing content focused guidance and adherence reminders. Guidance can be a beneficial factor of internet interventions (51) and can have a positive effect on treatment adherence (52). eCoaches are psychologists or psychotherapists in training, licensed psychotherapists or trained masters' level psychology students. eCoaches communicate with the participants via the messaging function on the platform. The main role of the eCoach is to motivate, guide participants, and monitor adherence to the treatment as well as risk for deterioration, crisis, or other adverse effects. Within 48 h of module completion, participants receive written feedback on each completed module. Feedback is based on a standardized eCoaching manual which contains preformulated standardized text blocks prepared for each session. The feedback will be individualized for each participant and each module. As adherence is monitored, if participants fail to complete a module within 7 days (14, 21 days) they will receive individualized reminder messages by the eCoach. After 28 days reminders will be sent via text message.

### Assessments

Clinician-based and self-report assessments will take place at screening (T0), baseline (T1), post-assessment 8 weeks after randomization (T2), 6-month follow-up (T3), and 12-month follow-up in the IC group (T4). There will also be weekly mood assessments during the first seven weeks of the study phase. See Figure 1 for a detailed overview of the study flow and Table 2 for an overview of all assessments. Clinician-based diagnostic assessments will be conducted via telephone.

**Table 2 T2:** Overview of self-report assessments.

**Construct**	**Questionnaire**	**T0**	**T1**	**T2**	**T3**
Demographics	Socio-demographic data (SozDemo)	✓	–	–	–
**PSYCHOPATHOLOGY**					
Depression	Center for Epidemiological Studies Depression Scale—Short Version (CES-D)^*^	✓	✓	✓	✓
Anxiety	General Anxiety Disorder Measurement (GAD-7)^*^	✓	✓	✓	✓
Depression	Patient Health Questionnaire (PHQ-9)	–	✓	–	–
Alcohol abuse	The Alcohol Use Disorders Identification Test (AUDIT-C)	–	✓	✓	✓
**QUALITY OF LIFE**					
	EuroQol (EQ-5D)	–	✓	✓	✓
	Assessment Quality of Life (AQoL-8D)	–	✓	✓	✓
**RESOURCE USAGE**					
	Client Service Receipt Inventory (CSRI)	–	✓	–	✓
**TRAINING**					
Expectancy	Credibility Expectancy Questionnaire (CEQ)	–	✓	–	–
Negative treatment effects	Inventory to assess negative effects of psychotherapy (INEP)	–	–	✓	–
Program evaluation	Client Satisfaction Questionnaire (CSQ-8)	–	–	✓	–
**OTHER**					
Moderators of treatment outcome	Risk Factor Questionnaire (RFQ)	–	✓	–	–
Worry	Penn State Worry Questionnaire—Ultra Brief (PSWQ-3)	–	✓	✓	✓
Sleep	One item of Pittsburgh Sleep Quality Index (PSQI)	–	✓	✓	✓
Emotion regulation	Subscales of emotion regulation scale questionnaire (SEK−15)	–	✓	–	–
Incongruence	Incongruence questionnaire—short version (INK-K)	–	✓	✓	✓
Personality	Big Five Inventory (BFI-10)	–	✓	–	–
Behavioral activation	The Behavioral Activation for Depression Scale (BADS-FS−9)	–	✓	✓	✓
Intervention drop-out reasons	Drop-Out Reasons (DG)	–	–	✓	–
Other help	Other help (INH)	–	–	✓	–

T0, screening; T1, baseline; T2, post-assessment; T3, 6-month follow-up.

* *CES-D and GAD-7 assessed weekly until post-assessment*.

Adherence to assessments completion will be monitored throughout the study. In case of noncompliance, study participants will be contacted after 7 (14, 21) days to remind them of assessment completion. After 28 days short messages will be sent via mobile phone.

#### Primary outcome

The primary outcome will be clinician-based ratings of depressive symptom severity at post-assessment (T2). Clinician-rated depressive symptom severity will be assessed by the QIDS-C (53) which covers nine criteria with 16 items: sleep, sad mood, appetite/weight, concentration/decision making, self view, thoughts of death or suicide, general interest, energy level, and restlessness/agitation. The items are each rated from 0 to 3. A meta-analysis found Cronbach's alpha to be acceptable to good (α = 0.69 − 0.89) (54). Trained psychologists' who are blind to treatment condition will conduct the diagnostic interviews. Interrater reliability will be examined by rating interviews a second time of ~10% of participants by a second rater. Several measures will be taken to ensure blinding: (1) explaining to the participant the importance of keeping the interviewers blinded to randomization status, (2) verbal reminder before each assessment, (3) documentation after each assessment whether the assessor is still blind to study condition.

#### Secondary outcomes

##### Psychopathology

Secondary outcome measures include a clinician-based change in diagnostic status (depression and anxiety), clinician-rated symptom severity of anxiety, and self-report symptom severity of anxiety and depression, the number of participants that responded and in remission, substance use, sleep quality, quality of life, and others.

Diagnostic status will be assessed at baseline, post-assessment, 6-month follow-up and 12-month follow-up (only in the IC) by sections of the MINI covering depression and anxiety (social phobia, generalized anxiety disorder, panic, agoraphobia) (48). Self-reported depression symptom severity referring to the previous week will be assessed by the Center for Epidemiological Studies Depression Scale (CES-D; 20 items, item range 0–3; reliability α = 0.95) (55, 56). The Patient Health Questionnaire (PHQ-9; 9 items; item range 0–3; reliability α = 0.89) (57– 61). The SIGH-A, a clinician-based anxiety rating, is used to assess anxiety severity (SIGH-A; 14 items; 0–4; reliability α = 0.89) (62). Anxiety is also measured in self-report by the generalized anxiety disorder measurement (GAD-7; 7 items; item range 0–3) (61).

To evaluate response and remission rates, participants will be coded as responders when they demonstrate a symptom reduction of 50% assessed by CES-D or GAD-7 respectively. Remission is defined a priori as a non-pathological score of ≤6 for the QIDS-C (53).

Other measures included alcohol consumption use (AUDIT-C; 3 item; item range 0–4 reliability α = 0**.**61) (63, 64), worrying (PSWQ-3; 3 items; item range 0–6; α = 0**.**85) (65, 66), sleep quality (PSQI; 1 item; item range 1–4; α = 0**.**74) (67, 68), behavioral activation (BADS-FS; 9 items; item range 1–6; α = 0**.**73) (69– 71), and quality of life [AQoL-8D; 35 items; item range1–5; α = [0.69–0.90] (72); EQ-5D-5L; 5 items plus 1 scale; item range 1–5; α = [0.51–0.96] (73– 75)].

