The aim of the present study is to evaluate the efficacy, moderators, and cost-effectiveness of a transdiagnostic individual participant tailored internet-based mobile-supported guided intervention for depression and anxiety in individuals with MDD with and without comorbid anxiety.

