#### Assessment of eligibility and randomization

Individuals interested in study participation will receive a detailed email with information on the study procedure. The applicants are then asked to complete an online screening containing question on demographic information, current state and history of mental health, and experience with psychotherapeutic treatment. Individuals who show symptoms of depression (CES-D ≥ 16) and do not fulfill any of the exclusion criteria will receive detailed study information and are requested to acknowledge and sign the consent form. The signed consent form can be sent by postal mail or email. Following informed consent, diagnostic interviews will be conducted by trained diagnostic assessors. Individuals who fulfill all inclusion criteria and no exclusion criteria proceed to complete baseline assessments. Once these are completed, individuals are included in the study and randomized to one of the study conditions, the guided intervention (IC) or the wait-list control (WLC) group.

Randomization will take place at an individual level by an independent researcher not otherwise involved in the study administration. A randomization list is created in a 1:1 ratio based on sequences of 8 per block using an automated computer-based random integer generator (randlist). Until randomization is completed, allocation will be concealed from participants, researchers involved in study administration, and eCoaches. eCoaches are psychologists or psychotherapists in training, licensed psychotherapists, or trained masters' level psychology students providing support to the participants during the duration of the online training. Outcome assessors will remain blind throughout the study. After randomization, participants will be informed of the outcome, and participants in the IC will receive immediate access to the online treatment while participants randomized to the WLC will receive login access to the training 6 months after study intake.

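### Response is defined only on self-report and, for anxiety, without a baseline floor, while remission uses the assessor-blind QIDS-C

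*Protocol article*

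**What the plan says.** Under Secondary outcomes, Psychopathology, the article fixes response: "participants will be coded as responders when they demonstrate a symptom reduction of 50% assessed by CES-D or GAD-7 respectively". The next sentence fixes remission on another scale: "Remission is defined a priori as a non-pathological score of ≤6 for the QIDS-C".

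The same section gives the source of each scale:
- CES-D: "Self-reported depression symptom severity referring to the previous week will be assessed by the Center for Epidemiological Studies Depression Scale".
- GAD-7: "Anxiety is also measured in self-report by the generalized anxiety disorder measurement".
- SIGH-A: "The SIGH-A, a clinician-based anxiety rating, is used to assess anxiety severity". No response criterion is attached to it.

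On blinding, the section on eligibility and randomization says of participants: "After randomization, participants will be informed of the outcome". The comparator is a wait-list. Of the raters it says: "Outcome assessors will remain blind throughout the study". The Primary outcome section adds that the QIDS-C interviewers are blind to condition and lists three measures to protect this.

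On the population, the stated aim covers "individuals with MDD with and without comorbid anxiety". The only symptom threshold for entry is a CES-D score of at least 16 at screening, and there is none for anxiety.

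Under Clinical analyses, response and remission rates are both compared with contingency tables and χ2. Cohen's d and NNT are announced for the comparison of primary and secondary outcomes, without naming the binary outcome behind the NNT.

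**The concern.** Response and remission are normally read as a pair: how many improved substantially, and how many became well. Here one comes from the participant and the other from a blinded rater on a different instrument. If the two between-arm differences diverge, the reader cannot tell whether that reflects depth of improvement, the scale, or who did the rating. The trial takes care to blind its raters, yet the response rule makes no use of their ratings.

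The anxiety rule has a second weakness. A percentage reduction behaves sensibly only when there is something to reduce. With no floor and no restriction, participants who start with few anxiety symptoms can become responders through ordinary fluctuation of one or two points. A participant who starts at 0 cannot be classified at all. The anxiety response rate would then partly count people for whom response has little meaning.

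**Working it through.** **1. Definitions side by side**

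| Outcome | Scale | Who rates | Rater knows allocation? |
|---|---|---|---|
| Depression response | CES-D, 50% reduction | participant | yes |
| Anxiety response | GAD-7, 50% reduction | participant | yes |
| Remission | QIDS-C ≤6 | interviewer | no |
| Primary outcome | QIDS-C at T2 | interviewer | no |
| Anxiety severity | SIGH-A | clinician | no (outcome assessors stay blind) |

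Response is the only clinical improvement rate in the plan that rests solely on self-report. No response is defined on the QIDS-C or SIGH-A.

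**2. Arithmetic of the GAD-7 rule**

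The rule is (T1 − T2)/T1 ≥ 0.50.
- T1 = 2, T2 = 1: (2 − 1)/2 = 0.50, so a one-point change is a response.
- T1 = 0: the denominator is 0 and the rule has no value.

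The CES-D rule is less exposed, because entry requires a CES-D of at least 16 at screening.

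**3. How fragile the rule is at low baselines (assumed inputs)**

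The article gives no baseline GAD-7 distribution, no SD of change and no response rates, so this shows a pattern and is not an estimate for the trial. Assume no true mean change in either arm, normally distributed change with SD s between 2 and 4 points, scores rounded to whole points, and a reporting shift of δ = 1 point in the intervention arm only. For an even baseline b, a responder has a rounded T2 score of b/2 or less, so

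P(response) = Φ((0.5 − b/2 + δ)/s).

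| Baseline b | s | No shift (δ = 0) | 1-point shift (δ = 1) | Spurious difference |
|---|---|---|---|---|
| 4 | 2 | Φ(−1.5/2) = 22.6% | Φ(−0.5/2) = 40.0% | 17.4 points |
| 4 | 4 | Φ(−1.5/4) = 35.3% | Φ(−0.5/4) = 45.1% | 9.7 points |
| 12 | 2 | Φ(−5.5/2) = 0.3% | Φ(−4.5/2) = 1.2% | 0.9 points |
| 12 | 4 | Φ(−5.5/4) = 8.4% | Φ(−4.5/4) = 13.1% | 4.8 points |

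The percentages are simulated values; the formula agrees with them to about 0.1 point. At a baseline of 4, chance alone makes about a quarter to a third of participants responders, and a one-point reporting shift adds 10 to 17 points. At a baseline of 12 the same shift adds 1 to 5 points. The rule is least stable where there is least anxiety to treat.

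**4. What is untouched**

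The plan's own figures do not involve response and they reproduce. For d = 0.73, one-sided alpha 0.05 and 80% power, the t-test needs 23.9, so 24 per arm and 48 in total. At 100 per arm the detectable d is 0.353, against the stated 0.35.

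**The case against.** Several points on the other side carry weight.

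**Blinded binary outcomes already exist.** Remission is on the QIDS-C, and clinician-based change in diagnostic status covers both depression and anxiety. The cost-effectiveness analysis uses disorder-free participants and not response. This stands, and it limits the importance of the point.

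**Self-report is a deliberate complement.** The Discussion presents interviews together with self-report as a strength, and the scales are named in advance. This also stands, and is why CES-D and GAD-7 response should be kept. It does not explain why the only response rates should be the self-reported ones.

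**Assessor blinding does not remove expectation.** The QIDS-C is rated from a telephone interview with someone who knows their allocation. A reader might infer that a QIDS-C response would be free of expectation bias, or that the QIDS-C was chosen to avoid it. The article supports neither; blinding removes only the rater's knowledge.

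**The GAD-7 restriction may be set elsewhere.** The article does not say that GAD-7 response is computed for everyone; that follows only from the absence of a restriction. A fuller plan may state a subset. The wording most naturally gives separate depression and anxiety rates, so this part touches the anxiety rate alone. The rule as printed is still incomplete for a baseline of 0.

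**The NNT.** A reader might infer that the reported NNT will be biased because response is self-reported. The article does not tie the NNT to response; it could come from QIDS-C remission or diagnostic status. It would share the weakness only if response were used.

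**Size.** One might apply the 53% comorbidity estimate quoted in the Introduction and conclude that 200 × (1 − 0.53) = 94 participants have no anxiety to respond with. That is a general epidemiological figure and not a forecast for this sample, and having no anxiety diagnosis is not the same as having no GAD-7 symptoms.

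**Conclusion.** The point holds in a limited form. Response rests only on self-report by participants who know their allocation, while remission rests on the assessor-blind QIDS-C, so two rates tested in the same way come from different scales and raters. As printed, the GAD-7 rule has no floor and no anxiety subset in a trial that enrols people without comorbid anxiety: small changes at low baselines count as response and a baseline of 0 is undefined.

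The size of any bias cannot be derived from the document. The spurious differences of 10 to 17 points at a low baseline and 1 to 5 points at a higher one depend wholly on the assumed SD of change, the absence of true change and the assumed one-point reporting shift. The documents do not support the stronger conclusion that the trial's NNT is biased. The primary outcome, its analysis, the sample size and remission are unaffected. This is an inexpensive improvement to a stated secondary rule.

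**What to change.** In the Psychopathology section and under Clinical analyses:

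1. Define the main depression response as a reduction of at least 50% in QIDS-C from T1, and keep CES-D response as supportive.
2. Define anxiety response as a reduction of at least 50% on the SIGH-A, with GAD-7 response supportive, among participants with a MINI anxiety disorder at T1. State how a zero or very low T1 score is handled.
3. Name the binary outcome behind each NNT, and base any response NNT on the QIDS-C definition.

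The cost is a change of text, provided the QIDS-C and SIGH-A are rated at T1 as well as T2. The article schedules clinician-based assessments at both visits but does not list these two scales visit by visit. The drawback is a smaller and less precise sample for anxiety response; its size depends on the share with an anxiety disorder at T1, which the article does not give for this trial. The change aligns response with the primary outcome and remission in scale and rater, but leaves participants' own expectations in place, and the report should say so.

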##### Weekly mood assessments

Depressive and anxiety symptoms will be measured weekly with the CES-D and GAD-7 from baseline (week 1) to post-assessment (week 8). This allows a temporally more precise assessment of mood rating of the IC group compared to the WLC during the intervention phase.

##### Training acceptability and adherence

User satisfaction with the training will be assessed after the intervention phase using the Client Satisfaction Questionnaire (CSQ-8; 8 items; item range 1–4; reliability α = 0.91) (76) adapted to the online context (77). Other assessments related to the training include the credibility expectancy questionnaire (CEQ) (78, 79), and a questionnaire on negative effects of online training (adaption of Inventar zur Erfassung Negativer Effekte von Psychotherapie—INEP) (80). Adherence to session completion is tracked throughout the intervention by the training platform.

##### Resource usage

To assess the impact of the intervention on publicly-funded services and the wider society, individuals' use of services, and societal impacts such as productivity loss will be gathered by the Client Service Receipt Inventory (CSRI) adapted to the German and Swiss Health Care System (81).

#### Predictors and moderators of disorder course and treatment outcome

Predictors and moderators of treatment outcome and factors associated with the development and maintenance of MDD and anxiety will be assessed at baseline. These are based on a recent review of factors such as symptoms and other easily-assessed clinical features predicting long term treatment outcome in MDD (47), as well as a literature search [search terms in PubMed in June 2016: “risk factor” AND (“depression” OR “anxiety”)] on factors predicting onset or maintenance of MDD. Predictors and moderators of treatment outcome could help explain treatment heterogeneity (47). Predictors and moderators will be assessed in the demographic questionnaire, through the aforementioned clinical assessment instruments, and in a risk factor questionnaire (RFQ).

##### Demographic information

A demographic questionnaire will, among other sociodemographic information, assess age, gender, education, migration status, height, weight, ethnicity, current job situation, size of household, income, sexual orientation, and religiosity/spirituality.

##### Mental health

Additional mental health assessments will include 16 items from validated instruments, and cover perceived stress (82), anxiety sensitivity, (83), need for affect (84), worry (65), resilience (85), energy levels, and suicide attempts.

##### Stressful life events and trauma

Stressful childhood and lifetime events will be assessed by approximately 38 items using the Childhood Trauma Questionnaire (86), family pathology and suicidality, experiences of abuse, accident involvement, experiences of discrimination, the List of Threatening Life events (87), and job satisfaction.

##### Lifestyle

Lifestyle will be assessed by the Simple Physical Activity Scale (SIMPAQ) (88) which assesses hours of sleep, physical activity, exercise, and sedentary behavior in the previous week as well as subjective diet quality, diet satisfaction, smoking, and drug usage habits.

##### Self-image

Aspects of self-image will be covered by 17 items, including two on self-esteem (89), body satisfaction assessed by the Eating Disorder Examination (90), and perceived social and minority status.

##### Relationship satisfaction and loneliness

Relationship satisfaction will be assessed by the 10 item short version of the relationship satisfaction questionnaire (91), and loneliness will be assessed by the three item scale (92).

##### Other assessments

Other assessments will include subjective sleep quality assessed by the Pittsburgh Sleep Quality Index (PSQI) (93), chronic medical conditions, the five items of the Sense of Mastery questionnaire (94), 23 item short version of the incongruence questionnaire (95), the assessment of behavioral activation (BADS-FS) (70), the ultra-short version of the Big Five Inventory (BFI-10) (96), and various emotion regulation skill scales (subscales comprehension, acceptance, and emotional self-support by the German Emotion Regulation Scale Questionnaire, ERSQ-27, ERSQ-ES-GD) (97, 98).

### Statistical analyses

Statistical analyses will be reported in accordance with the statement by Consolidated Standards of Reporting Trials (CONSORT) (99).

#### Clinical analyses

Data analysis will be performed on an intention-to-treat (ITT) basis. Additionally, per protocol analysis including only participants who have completed the primary outcome will be analyzed. Missing data will be handled by multiple imputations (MI) with 100 iterative estimations per value, as this is currently regarded as the gold standard with regard to missing data (100). Demographic variables as well as other baseline variables will be inserted into the prediction model to estimate missing values. Differences in the primary and secondary outcomes between the two study groups will be examined with repeated measurements analysis of variance, and standardized effect sizes (Cohen's *d*) and number needed to treat (NNT) and their respective confidence intervals will be calculated for comparison. Response and remission rates will be compared across groups with contingency tables and differences tested with χ2. All unidirectional hypotheses will be tested one-sided, bidirectional hypotheses will be tested two-sided. Alpha is set to *p* < 0.05. All analyses will be conducted with SPSS.

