#### Predictor and moderator analyses

Predictors and moderators of treatment outcome will be analyzed on an exploratory basis with a priori defined potential moderators: sociodemographic factors such as gender, age, income, education, ethnicity, socioeconomic status, education level, status of employment, relationship status, sexual orientation, religious, and spiritual orientation, current and previous mental health including age of MDD onset, MDD severity, low energy, number of previous episodes, duration of episodes, MDD chronicity, concurrent antidepressant use, current/past suicidality, suicide attempts, comorbid anxiety, anxiety sensitivity, substance use, perceived stress, insomnia/sleep problems, rumination, need for affect, sense of mastery, self-esteem, resilience, self-regulation, quality of life, experience with psychotherapy, physical health including diet, weight, body mass index, body satisfaction, number of medical conditions, physical functioning, sedentary behavior, smoking, drug use, quality of life, life events including childhood maltreatment/trauma, and life events, minority, and perceived social status, discrimination, experience of abuse, parental and familial psychopathology, social environment, social support/relationships, relationship satisfaction, loneliness, personality traits such as neuroticism and openness to experiences, and psychological coping skills such as emotion regulation skills. Regression analyses will be used to test interaction effects between baseline moderators and the intervention condition, using the SPSS macro PROCESS (102). Significant interactions will further be investigated applying the Johnson-Neyman technique to detect the region of significance (103).

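### The imputation model for the ITT analysis names only baseline predictors, so if followed as written it shrinks the treatment effect roughly by the fraction of T2 data missing

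*Protocol article*

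**What the plan says.** All references are to the protocol article.

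- **Clinical analyses:** "Data analysis will be performed on an intention-to-treat (ITT) basis", and "Missing data will be handled by multiple imputations (MI) with 100 iterative estimations per value". The predictors are then described: "Demographic variables as well as other baseline variables will be inserted into the prediction model to estimate missing values".
- **Clinical analyses, comparison:** "Differences in the primary and secondary outcomes between the two study groups will be examined with repeated measurements analysis of variance". The supplementary analysis is restricted to participants with an observed primary outcome ("per protocol analysis including only participants who have completed the primary outcome will be analyzed").
- **Primary outcome:** "The primary outcome will be clinician-based ratings of depressive symptom severity at post-assessment (T2", measured by the QIDS-C.
- **Assessment of eligibility and randomization:** participants complete the baseline assessments first and are randomized afterwards. Arm is therefore not a baseline variable in the protocol's own sequence.
- **Weekly mood assessments:** "Depressive and anxiety symptoms will be measured weekly with the CES-D and GAD-7 from baseline (week 1) to post-assessment (week 8"). The section presents these scores as a comparison of the two arms.
- **Predictor and moderator analyses:** "Regression analyses will be used to test interaction effects between baseline moderators and the intervention condition". The section calls these analyses exploratory and does not mention imputation.

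**The concern.** An imputation model should contain every term of the analysis it feeds, plus good predictors of the missing value and of dropout. The analysis here compares two arms, and the list of imputation predictors does not include arm. Imputed values from such a model carry no treatment effect beyond what baseline explains, and under randomization that is nothing on average. Averaging them with the observed values pulls the arms together.

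The second gap is the weekly scores. If people leave because of how they are doing during the eight weeks, baseline variables cannot account for it. The weekly CES-D and GAD-7 partly can, and the trial collects them. The protocol's Introduction itself lists higher dropout among the challenges of internet interventions. The completer analysis does not help here, because it conditions on the same dropout.

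At stake are the primary ITT estimate and the Cohen's d, NNT and confidence intervals derived from it.

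**Working it through.** **1. The protocol's own figures (Power and sample size calculation).** For d = 0.73, one-sided alpha 0.05 and 80% power, the calculation gives 24 per arm, 48 in total, with noncentral-t power of 80.1%. This matches the text. With 100 per arm the detectable effect is (z0.95 + z0.80) × √(2/100) = 0.352, against the stated 0.35. Power at d = 0.35 is 79.4%.

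**2. Imputation without arm.** Let m1 and m0 be the fractions missing at T2 in the intervention (IC) and wait-list (WLC) arms, with missingness unrelated to outcome given baseline. The observed pool contains IC participants in the proportion p = (1 − m1)/(2 − m1 − m0), so every imputed value carries p × d of the effect. After imputation:

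- IC carries (1 − m1)d + m1·p·d.
- WLC carries m0·p·d.
- The difference is d × 2(1 − m1)(1 − m0)/(2 − m1 − m0).

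With m1 = m0 = m this reduces to d(1 − m). No correlation has to be assumed. The missing fractions below are assumptions.

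| Missing per arm | d = 0.73 becomes | d = 0.35 becomes | Power at N = 200 for the latter |
|---|---|---|---|
| 0% | 0.73 | 0.35 | 79% |
| 10% | 0.657 | 0.315 | 72% |
| 20% | 0.584 | 0.280 | 63% |
| 30% | 0.511 | 0.245 | 53% |

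Power reflects the smaller effect only; information lost through missing data is not counted. With unequal missingness of 30% and 10%, the factor is 2 × 0.7 × 0.9/1.6 = 0.788, so 0.73 becomes 0.575.

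**3. Dropout that depends on symptoms during treatment.** This was a large-sample simulation (n = 200,000). Assumed correlations: baseline with T2 0.4, baseline with weekly score 0.4, weekly score with T2 0.7. The assumed effect on the weekly score was 0.6d, and dropout was logistic in the weekly score with slope 1. True d = 0.73, 20% missing overall:

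| Who drops out | Baseline only | Baseline + arm | Baseline + arm + weekly |
|---|---|---|---|
| At random | 0.593 | 0.738 | 0.739 |
| Worse, both arms | 0.562 | 0.700 | 0.728 |
| Worse in IC | 0.657 | 0.825 | 0.735 |
| Better in IC | 0.490 | 0.615 | 0.728 |
| Worse in IC, better in WLC | 0.730 | 0.919 | 0.730 |

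Across these five mechanisms at 10, 20 and 30% missing (15 cases), the baseline-only model fell below the truth in 13, was unchanged in one (0.730) and was marginally above it in one (0.743). Adding arm alone removes the shrinkage of step 2 but leaves dropout bias, from 0.615 to 0.919 at 20% missing.

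**4. A more unfavourable case.** The same correlations were used, with worse IC participants dropping out and WLC dropout at random. For a true d of 0.50 with 32% against 12% missing, the baseline-only model gives about 0.50, because shrinkage and dropout bias nearly cancel. Baseline + arm gives about 0.64. Under a true null with 42% against 12% missing, baseline-only gives about 0.13 and baseline + arm about 0.19. Steeper dropout slopes (1.5 and 2.5) raise the baseline-only results to about 0.53 and 0.56, and under the null to about 0.17 and 0.21.

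**5. Limit of the remedy.** If 70% of those missing T2 also lack the weekly score (an assumption), and it is used only where observed, the slope-1 cases in step 4 give about 0.60 for a true 0.50 and 0.13 under the null. With the weekly score fully observed they give about 0.50 and 0.00.

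**The case against.** The strongest reply is that the sentence is not exclusive. It says which variables go in, not that nothing else does, and a journal article condenses. By-arm imputation and a full auxiliary list often sit in an analysis plan, which is not shown here. A reader might infer that the protocol rules out arm and post-baseline scores; the documents do not support that. What stands is narrower: the protocol chose to describe the predictors, every one it describes is a baseline variable, and an analyst following the text would fit a model without arm. That is more than silence on a detail.

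A reader might also infer that the plan will inflate the effect. That does not follow either. Omitting arm shrinks it. The large upward errors in the working (0.825, 0.919, and about 0.64 for a true 0.50) come from a model that includes arm and lacks the weekly scores, which is not the model the text describes. Under the described model, upward bias needs strong dropout that depends on symptoms and differs by arm.

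Three further points are fair. The completer analysis would expose shrinkage caused by imputing without arm, although it would not correct outcome-related dropout. The weekly scores are online self-reports, and the protocol itself anticipates assessments not being completed, so people who miss T2 may lack them too. The moderator analyses are exploratory and are not said to use imputed data, so dilution of the interactions is conditional on that.

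**Conclusion.** The point holds in limited form. The imputation model as described does not match the between-arm analysis it serves. If followed, it attenuates the primary ITT effect by about the missing fraction: 10 to 30% attenuation for an assumed 10 to 30% missing, equal by arm and unrelated to outcome given baseline. At d = 0.73 the trial keeps ample power with N = 200, and the harm is to the estimate. At d = 0.35, the effect the protocol says N = 200 can detect, power is lost as well.

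Bias from dropout related to symptoms during treatment is a second consequence. Its direction and size depend on who drops out. The protocol gives no dropout rate, correlation or mechanism, so every magnitude beyond the d(1 − m) formula is illustrative. This should be corrected before analysis, unless a fuller plan already specifies arm and post-baseline scores.

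**What to change.** In Clinical analyses, state that:

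- imputation is done separately by arm, or the model includes arm and its interactions;
- the model includes baseline QIDS-C, the weekly CES-D and GAD-7 scores, and the available T2 and T3 clinician-rated and self-report scores as auxiliary variables, in addition to the demographic and baseline variables already named;
- if moderator models are run on imputed data, the imputation is by arm or contains the arm × moderator term.

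Adding arm alone is not enough, because it leaves dropout bias in place. The weekly scores help only to the extent that they are observed in participants who miss T2, so their completeness in that group should be reported.

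The cost is a change of wording and slightly more programming, with no new data. If a fuller plan already specifies such a model, the text only needs to be aligned with it.
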